# Study Protocol and Baseline Cardiometabolic Characterization of the RIO-Study (Response to an Intervention with Omega-3): A Randomized, Double-Blind, Placebo-Controlled Crossover Trial on Lipid and Inflammatory Profiles in Overweight and Obese Adults with Hypertriglyceridemia in Valdivia, Chile

**DOI:** 10.3390/nu17213397

**Published:** 2025-10-29

**Keywords:** cardiometabolic risk, dyslipidemia, inflammation, omega-3 fatty acids, overweight

## Abstract

Background: Cardiovascular diseases (CVDs) are the leading cause of morbidity and mortality worldwide, with metabolic syndrome and its risk factors contributing substantially to cases in Latin America. In southern Chile, obesity, dyslipidemia, and sedentary behavior are highly prevalent, yet comprehensive baseline data on these factors are scarce. Establishing regional cardiometabolic profiles is crucial to inform prevention strategies. Objective: To describe the RIO-Study protocol and characterize the baseline cardiometabolic profile of adults from Valdivia, southern Chile. Methods: The RIO-Study is a randomized, double-blind, placebo-controlled, crossover clinical trial evaluating the effects of nutritional doses of seaweed-derived omega-3 fatty acids on lipid metabolism, inflammation, and molecular lipid regulators in adults with overweight/obesity. The protocol includes a standardized high-fat breakfast challenge and repeated postprandial blood sampling to assess dynamic lipid responses. Screening procedures comprised blood pressure measurement, fasting blood sampling, body composition by bioelectrical impedance, and health and lifestyle questionnaires. Results: Among screened participants, 91% presented overweight/obesity and 55% presented central adiposity, exceeding regional cardiometabolic risk thresholds (waist circumference ≥ 90 cm in men, ≥80 cm in women). Men exhibited higher waist circumference (100 ± 10.8 vs. 91.6 ± 11.9 cm), waist-to-hip ratio (0.99 ± 0.08 vs. 0.92 ± 0.07), systolic blood pressure (130 ± 12.0 vs. 122 ± 13.4 mmHg), triglycerides (168 ± 84.7 vs. 122 ± 64.9 mg/dL), VLDL-C (33.7 ± 17.2 vs. 24.4 ± 13.0 mg/dL), and sedentary time (8.1 ± 2.3 vs. 6.8 ± 2.3 h/day). Women had greater total body fat (39.7 ± 4.75% vs. 31.1 ± 5.30%), higher HDL-C (56.6 ± 13.3 vs. 46.9 ± 9.39 mg/dL), and more often had normal weight (13% vs. 0%). Conclusions: The RIO-Study provides novel insights into cardiometabolic risk and will elucidate the effects of nutritional omega-3 supplementation in a high-risk Chilean population.

## 1. Introduction

Cardiovascular diseases (CVDs) represent a global health crisis, claiming approximately 17.9 million lives annually through a complex interplay of behavioral, metabolic, and genetic risk factors [1]. At the center of this burden is metabolic syndrome (MetS), a constellation of conditions including central obesity, dyslipidemia, hypertension, and hyperglycemia that significantly increases cardiovascular risk [2]. Among these, elevated fasting or postprandial triglyceride levels have emerged as independent predictors of CVD events, making them a critical therapeutic target [3]. The Latin American region, particularly Chile, exemplifies the global shift toward higher cardiometabolic risk. The country has experienced a dramatic increase in overweight and obesity, currently affecting 78.8% of adults (≥15 years), paralleled by increasing rates of central adiposity and MetS [4]. This epidemic is explained by unhealthy sedentary behaviors, with widespread failure to meet established “24-h movement guidelines” which encompass adequate physical activity, limited sedentary time, and sufficient sleep. Non-adherence to these guidelines correlates strongly with high risks of obesity, hypertension, dyslipidemia, type 2 diabetes, MetS, and long-term cardiovascular complications [5]. However, comprehensive Latin American data characterizing cardiometabolic profiles remains limited, particularly in southern Chile [6].

Omega-3 polyunsaturated fatty acids (PUFAs), notably eicosapentaenoic acid (EPA) and docosahexaenoic acid (DHA), have attracted considerable attention for their well-documented lipid-lowering and anti-inflammatory properties [7,8,9], establishing them as promising interventions for cardiometabolic risk reduction. Nevertheless, the therapeutic efficacy of omega-3 supplementation exhibits substantial interindividual variation, influenced by baseline metabolic status, dietary patterns, genetic architecture, and lifestyle factors [10,11]. While omega-3 research has flourished in high-income countries, intervention studies targeting Latin American populations remain sparse [12]. The RIO-Study trial was designed to address this knowledge gap.

Therefore, this work aims to (1) describe the design and methodology of the RIO-Study and (2) characterize the baseline cardiometabolic profile of adults from Valdivia, Chile, assessed during the screening phase.

## 2. Materials and Methods

### 2.1. Trial Design

The RIO-Study (Response to an Intervention with Omega-3 Fatty Acids on Lipid and Inflammatory Profiles in Overweight and Obese Individuals with Hypertriglyceridemia in Valdivia, Chile) is a randomized, double-blind, placebo-controlled, two-period, two-sequence crossover trial. Each participant completed two supplementation phases of six weeks, separated by a 10-week washout period to minimize carryover effects (Figure 1). Recruitment was conducted between July 2024 and June 2025 at Universidad San Sebastián, Valdivia, Chile. This study was initially approved by the Scientific Ethics Committee of Universidad San Sebastián (CEC-USS, No. 42-24, 11 April 2024). Subsequently, the Scientific Ethics Committee of the Los Ríos Health Service (No. 186, 12 June 2024) provided oversight of protocol amendments, which, in accordance with its procedures, were reported collectively upon study completion.

### 2.2. Recruitment

Participants were recruited through social media, posters, local radio announcements, and printed graphics displayed throughout the city. Informative sessions were held to present the study objectives, procedures, potential risks and benefits, and to address participants’ questions prior to obtaining written informed consent. Following their consent, participants attended a screening visit to verify their eligibility according to the inclusion and exclusion criteria. As part of the informed consent process, participants also signed an agreement authorizing the storage of their biological samples (serum, plasma, and peripheral blood mononuclear cells (PBMCs)) at Universidad San Sebastián (Valdivia, Chile) for future analyses.

### 2.3. Participants

Eligible participants were adults aged 18–65 years, with a body mass index (BMI) between 25.0 and 34.9 kg/m^2^, and fasting triglycerides between 100 and 215 mg/dL. Exclusion criteria included the following: BMI < 25 or >34.9 kg/m^2^; significant weight change (≥10% in the previous three months); fasting triglycerides > 215 mg/dL; blood pressure > 140/90 mmHg; presence of uncontrolled metabolic or chronic diseases (hypertension, dyslipidemia, type 2 diabetes), pregnancy/lactation, and allergies or intolerances to study products (lactose, wheat, seaweed, and sunflower oil); use of triglyceride-lowering drugs (e.g., Fibrates) or anticoagulants; recent blood donation (last 3 months); and excessive alcohol consumption (≥40 g daily).

### 2.4. Intervention

Each participant received both treatments in random order. The intervention consisted of one capsule per day containing 1 g of lipid extract from AlmegaPl^®^ 2515 (Qualitas Health Inc., Houston, TX, USA, operating under iwi life), an EPA-rich (250 mg/d EPA) oil derived from microalgae *Nannochloropsis* sp. against a placebo control treatment consisting of high-oleic sunflower oil (HOSO). HOSO was selected as the control oil because it is rich in monounsaturated fatty acids and contains very low levels of omega-6 linoleic acid, thereby minimizing potential confounding from n-6–derived metabolites while providing a metabolically neutral comparator, in omega-3 intervention effects.

Capsules were identical in size, weight, and packaging to ensure blinding. Adherence was assessed by counting the returned capsules at each crossover visit (visit 2 and visit 4). Participants were also asked to report any adverse events during each visit.

### 2.5. Aims

The primary aim of this trial is to determine the effectiveness of omega-3 fatty acids at nutritional doses in improving fasting serum triglyceride levels. Secondary aims include postprandial serum triglyceride levels (0, 2, 4, and 6 h); the expression of lipid metabolism genes, such as peroxisome proliferator-activated receptor alpha (PPARα) and sterol regulatory element-binding transcription factor 1 (SREBP1c isoform), in peripheral blood mononuclear cells (PBMCs) during fasting and 4 h after eating; plasma concentrations of low-grade inflammatory markers, including tumor necrosis factor alpha (TNFα) and interleukin-6 (IL-6), assessed at fasting and 4 h postprandial; and the atherogenic properties of very-low-density lipoproteins (VLDLs) in the fasting state, including their relative richness in triglycerides, remnant cholesterol, apolipoprotein C-I, and apolipoprotein C-III, in individuals from the Chilean population.

### 2.6. Study Visits

Participants attended five scheduled appointments, including one screening visit and four intervention visits corresponding to the two crossover phases. The screening visit was conducted to verify eligibility criteria and obtain informed consent. The intervention visits included the following: V1: baseline visit to initiate the first supplementation phase and conduct fasting and postprandial assessments; V2: end-of-phase visit to complete the first supplementation period and return unused capsules; V3: crossover baseline visit, conducted after a 10-week washout, to initiate the second supplementation phase and conduct fasting and postprandial assessments; and V4: final visit to complete the second supplementation period, return unused capsules, and perform final assessments.

#### Standardized High-Fat Meal Challenge

To assess the triglyceride postprandial response, a standardized high-fat meal challenge, locally adapted from a previously validated postprandial lipid test protocol [13], was included as a voluntary component of the study. The clinical research team prepared the meal, which consisted of three slices (90 g) of white bread (Ideal^®^, Ilford, UK), 60 g of full-fat butter (Colun^®^, La Unión, Chile), and 20 g of raspberry jam (Tía Lía^®^, Valdivia, Chile). According to the manufacturers’ nutrition data, this breakfast provided approximately 716 kcal, comprising 51.8 g of total fat, 53.1 g of carbohydrates and 9.4 g of protein, corresponding to 65% of total energy from fat, with 30% from carbohydrates, and 5% from protein (Supplementary Table S1). The breakfast was consumed in the university cafeteria within 20 min, with up to 1 L of water permitted throughout the day. Postprandial waiting periods (2, 4, and 6 h) were spent on university premises to ensure participants remained on site for subsequent blood collections. All participants who completed the postprandial challenge received a snack.

### 2.7. Study Procedures

Blood pressure was assessed after a 5 min seated rest using a calibrated automated sphygmomanometer (Bokang BK6022, Wenzhou Bokang Instruments Co., Ltd., Wenzhou, China) on the non-dominant arm. Three readings were obtained at 2 min intervals; the mean values of the second and third readings were recorded.

Blood samples were collected at baseline, and 2, 4, and 6 h after the high-fat meal challenge by trained personnel via standardized venipuncture, following CLSI guidelines [14]. A Vacutainer^®^ system (Becton Dickinson, Franklin Lakes, NJ, USA) with a 21G/23G butterfly needle was used. The antecubital area was disinfected with 70% alcohol for ≥30 s before puncture, and tubes were filled in the recommended order: serum separator (BD Vacutainer^®^ SST™, no. 367983), EDTA (BD Vacutainer^®^ K2EDTA, cat. no. 367861), and CPT™ (BD Vacutainer^®^ Cell Preparation Tube, cat. no. 362753). Serum tubes were centrifuged 30 min post-collection (1500× *g* for 15 min); EDTA tubes were centrifuged within 1 h (1500× *g* for 20 min); and CPT tubes were centrifuged within 2 h for peripheral blood mononuclear cell isolation using a centrifuge with a swinging-bucket rotor. All aliquots (0.5 mL) were stored at −80 °C until analysis.

Body composition (lean mass (kg), fat percentage, and basal metabolic rate (kcal/day)) and weight were measured using a bioelectrical impedance analyzer (Rice Lake X-Contact 350, Rice Lake Weighing Systems, Rice Lake, WI, USA) while participants were barefoot and wearing light clothing; 0.8 kg was subtracted for clothing weight. Height was measured with a stadiometer (SECA 213) to the nearest 1 mm, with participants in the Frankfurt plane, without shoes or headgear.

As part of the Case Report Form (CRF) [15], Questionnaires quantified the Food Consumption Trends Survey, dietary recall, medical history, mealtime habits (chrononutrion), and physical activity levels through the International Physical Activity Questionnaire (IPAQ), which is a validated questionnaire quantifying walking, moderate, and vigorous activities in MET-minutes/week [16]. Sedentary behavior was evaluated through daily sitting time. Additional lifestyle information, including smoking status (yes/no), and dietary habits (food frequency questionnaire), where a nationally adapted instrument was used [17], were collected via structured interviews conducted by trained staff. The Quantified Food Consumption Trends Survey was administered only to participants included in the study, to characterize their baseline dietary patterns. No dietary data was collected during the screening visit.

#### Harms

Potential risks associated with participation in the RIO-Study are considered minimal. Blood sampling may cause mild discomfort, pain at the puncture site, or small hematomas, and rarely lead to infection or an allergic reaction to materials. The standardized high-fat test meal may produce transient gastrointestinal discomfort such as bloating, nausea, or indigestion. Daily supplementation with omega-3 (AlmegaPl^®^) or high-oleic sunflower oil (HOSO) may lead to mild gastrointestinal disturbances (nausea, diarrhea, stomach discomfort) and, in rare cases, allergic reactions in individuals with hypersensitivity to algae, sunflower, or other capsule ingredients. Interactions with anticoagulant medication are recognized, and individuals using such drugs are excluded from participation. Both interventions are manufactured under quality standards to minimize risks of contamination.

Adverse events will be systematically assessed at each study visit through direct questioning and spontaneous reporting by participants. All events will be classified by severity (mild, moderate, severe), relatedness to the intervention (unrelated, possibly related, probably related), and outcome (resolved, ongoing, serious adverse event). Any unexpected adverse event will be reported immediately to the principal investigator. The study team will monitor participants closely throughout the trial and provide appropriate care as needed.

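### The adverse-event scheme lists serious adverse event as a level of outcome, so a serious event fits two codes and its seriousness or its course can be lost

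*Protocol article*

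**What the plan says.** The scheme is set out in the Harms part of section 2.7 of the protocol article. It has three axes and applies to every event:

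- Severity: "All events will be classified by severity (mild, moderate, severe").
- Relatedness: "relatedness to the intervention (unrelated, possibly related, probably related").
- Outcome: "outcome (resolved, ongoing, serious adverse event").

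On collection, the same part says: "Adverse events will be systematically assessed at each study visit through direct questioning and spontaneous reporting by participants". Section 2.4 adds only that participants were asked about adverse events at visits. On escalation there is one sentence: "Any unexpected adverse event will be reported immediately to the principal investigator".

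The same part names the foreseen risks. Among them are, for blood sampling, that it may "rarely lead to infection or an allergic reaction to materials" and, for the capsules, "in rare cases, allergic reactions in individuals with hypersensitivity to algae, sunflower, or other capsule ingredients".

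**The concern.** Outcome and seriousness are different attributes of an adverse event. Outcome says what became of it, and seriousness says whether it met a threshold of consequence. The scheme makes seriousness an alternative to *resolved* and *ongoing*, as if a serious event could be neither. Every serious event must in fact be one or the other, or have some further course that the list does not name.

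What is at stake is the harms report. In a small trial of a product whose risks are described as minimal, whether any serious event occurred under each treatment is the main safety result. Under this scheme, a table with no serious events could mean that none occurred, or that those that occurred were coded by their course.

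**Working it through.** There is no figure in the plan to reproduce, and the sample size and power play no part. The check is whether the stated levels can hold the information they are meant to hold.

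**Step 1: states against levels.** Seriousness has 2 values (yes, no). Course, as the article names it, has 2 values (resolved, ongoing). Crossed, they give 2 × 2 = 4 states. The outcome axis has 3 levels.

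| True state | Codes that fit | What is lost |
|---|---|---|
| Not serious, resolved | *resolved* | nothing |
| Not serious, ongoing | *ongoing* | nothing |
| Serious, resolved | *resolved* or *serious adverse event* | seriousness, or course |
| Serious, ongoing | *ongoing* or *serious adverse event* | seriousness, or course |

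Both serious states fit two codes. With one code per event, neither can be recorded in full.

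**Step 2: can another axis recover it?** Severity runs from mild to severe and grades intensity. The article itself uses *serious* separately from *severe*, so a severe grade cannot stand in for seriousness. Relatedness concerns cause. Section 2.4 adds no classification. Nothing in the article's adverse-event text restores the lost item.

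**Step 3: effect on the count.** Suppose S serious events occur under a treatment and k of them are coded by their course. The reported count is S − k, which can lie anywhere from 0 to S.

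- If k = 0, the count is right and the course is known for none of the S events.
- If k = S, the course is known for all and the count is 0.

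**Step 4: illustration.** Section 3 gives 40 enrolled participants. Assume that all 40 form the denominator and that one participant has one serious event. Coded as serious, the figure is 1/40 = 2.5%. Coded by its course, it is 0/40 = 0%. Both the event and the miscoding are assumed.

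**Step 5: the reporting trigger.** Seriousness (yes, no) crossed with expectedness (expected, unexpected) gives 4 cells. The stated sentence covers the 2 unexpected cells, whether serious or not. It is silent on the serious and expected cell. That is as far as the text goes: silence in the article is not a rule that such events are left unreported.

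**The case against.** **The levels may not be single-choice.** The article does not say that the three terms exclude one another, and the case report form is not shown. If the form allows two boxes to be ticked, or already has a seriousness item, nothing is lost in practice. This stands as a limit on the consequence. It does not repair the published scheme, which sets *serious adverse event* among the outcomes and says nothing of multiple coding.

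**The count may be intact.** A reader might infer that serious events by treatment cannot be recovered at all. That goes too far. A coder who always gives *serious adverse event* priority preserves the count and loses only the course. Source notes, where kept, may also allow recoding.

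**Escalation.** A reader might further infer that only unexpected events are reported at once, so that a serious allergic reaction or infection, being foreseen, need not be. The document does not support this, for four reasons:

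- The sentence says any unexpected event. It gives one sufficient trigger and excludes no other.
- *Unexpected* is not defined. The listed harms are described as mild, transient or rare, so a serious form of one could reasonably be treated as unexpected.
- Section 2.3 excludes people with allergy or intolerance to study products, seaweed and sunflower oil included. This makes a serious capsule reaction in an enrolled participant arguably unexpected, although it does not cover unrecognised hypersensitivity or the blood-sampling risks.
- A serious-event reporting procedure is something a journal article commonly leaves to the full protocol.

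**Limited reach.** Harms are not among the primary or secondary aims in section 2.5, and no adverse-event data are given. Both are true, and they keep the point modest.

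**Conclusion.** The coding point holds. It is an error in a list the article writes out, not detail left to a fuller document: the outcome levels overlap, and following them as written drops either the seriousness or the course of every serious event. The conclusion assumes one outcome code per event and no separate seriousness item on the form. The article is consistent with both assumptions but confirms neither.

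The size is unknown. The 2.5% against 0% contrast shows only what a single coding decision could do with 40 participants. The effect is confined to the harms result. The fasting triglyceride analysis and the sample size are untouched.

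On escalation, the supportable statement is narrower: the one immediate-report trigger in the article turns on unexpectedness and does not mention seriousness. That wording needs reconciling with the full protocol's serious-event procedure. It is not evidence that serious expected events go unreported.

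**What to change.** 1. Record seriousness as its own yes/no item for every event.
2. Restrict outcome to the course of the event (resolved, ongoing and any further course the team needs), and remove *serious adverse event* from that list.
3. Recode any events already collected from source notes, before harms are reported and while treatment allocation is still concealed if possible. Report serious events by treatment from the new item.
4. Reconcile the sentence on immediate reporting with the serious-event procedure in the full protocol, so that the two agree on how seriousness and unexpectedness enter. If the case report form already separates seriousness from outcome, correcting the article's description is enough and steps 1 to 3 fall away.

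The cost is low: at most one added field, a reworded sentence or two, and recoding of what is likely to be a small number of events. The design and the efficacy analysis do not change.

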### 2.8. Future Determinations

Several laboratory analyses are planned with the biological samples collected during the trial. Serum triglyceride concentrations will be determined using an enzymatic colorimetric assay (GPO/PAP method without glycerol blank) in fasting and postprandial samples (0, 2, 4, and 6 h). Total RNA will be extracted from peripheral blood mononuclear cells (PBMCs) to evaluate the expression of lipid metabolism-related targets such as *PPARA* and *SREBP1c*, using cDNA synthesis followed by quantitative real-time PCR (qPCR), with normalization to housekeeping genes and quantification by the ΔΔCt method. Inflammatory biomarkers (TNFα, IL-6) will be assessed in fasting and 4 h postprandial plasma samples through enzymatic assays and ELISA. Very-low-density lipoprotein (VLDL) particles will be isolated from fasting plasma by density gradient ultracentrifugation and analyzed for triglyceride richness, remnant cholesterol, and apolipoproteins C-I and C-III content in order to characterize their atherogenic properties. In addition, stored samples may be used for exploratory determinations of other lipid-related or inflammatory biomarkers not originally specified in the project proposal; such analyses will remain hypothesis-generating and will be reported in future manuscripts.

